### Quantification of cardiovascular risk

Four established cardiovascular risk scores will be applied to the kidney transplant recipients at the time of transplantation: the Framingham risk factor score, the European Systematic Coronary Risk Evaluation (SCORE) equation, and two coronary risk equations that use the calibrated Framingham functions for the Spanish population, the REGICOR (Registre Gironí del COR (Gerona Heart Registry)) and DORICA (Dyslipidemia, Obesity, and Cardiovascular Risk) functions.

The Framingham risk score will be calculated using both the classic Framingham-Anderson equation [30] and the equation modified by Wilson [31]. These scores predict the risk of developing fatal or non-fatal coronary heart disease (CHD) within a 10-year time period in adults between the ages of 30-74 with no known previous history of CHD, stroke, or peripheral vascular disease. CHD includes angina pectoris, myocardial infarction, coronary insufficiency (unstable angina) and coronary heart death.

The original Framingham-Anderson equation includes the following risk factors: age, sex, systolic blood pressure, total cholesterol, HDL-cholesterol, diabetic status, tobacco smoking status and evidence of left ventricular hypertrophy on resting electrocardiogram (ECG). The Framingham-Wilson equation replaces the continuous measurements of systolic blood pressure, total cholesterol and HDL-cholesterol with categorical variables based on the risk categories of the Joint National Committee on Blood Pressure and the National Cholesterol Education Program (NCEP) [41-43]. It also takes into account information regarding diastolic and LDL-cholesterol levels, and does not include the diagnosis of left ventricular hypertrophy due to its high association with hypertension and the absence of standard, universally accepted ECG criteria.

The European SCORE was developed by the European Society of Cardiology in 2003 as an estimation of 10-year risk of fatal cardiovascular disease (CVD) in subjects between the ages of 24 and 80. The variables used to calculate this score include age, gender, total cholesterol, systolic blood pressure and current smoking status [33]. The main difference between the SCORE risk chart and the Framingham model is that it estimates the risk for all atherothrombotic cardiovascular manifestations, including stroke, heart failure, peripheral arterial insufficiency or certain aneurysms, and not just CHD. The SCORE charts are currently the CVD charts recommended by the European Societies [44] and the Spanish Interdisciplinary Committee for Cardiovascular Disease Prevention (CEIPC) [45]. The SCORE risk charts calibrated for Spain will be used [46].

Finally, the REGICOR [32] and the DORICA [34] charts are adaptations of the Framingham equation to the Spanish population characteristics. Like the Framingham equation, these functions estimate the risk of coronary mortality and morbidity using information about age, gender, total cholesterol, HDL-cholesterol, systolic and diastolic blood pressure and smoking habits, differentiating diabetic from non-diabetic patients.

Patients will be classified as high-risk patients when their ten-year risk of coronary heart disease is ≥20% according to Framingham [31], REGICOR [32] and DORICA [34] equations or when their ten-year risk of cardiovascular mortality is ≥5% according to the SCORE system [44].

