## Methods/Design

### Design and study population

Observational, retrospective and prospective cohort study of all adult (> 18 years) patients who underwent primary or repeated kidney transplantation with a graft from a cadaveric or living donor in the A Coruña Hospital (northwest Spain) between 1 January 1981 and 31 December 2008. Patients who had undergone simultaneous kidney-pancreas transplantation will be excluded from the analysis.

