### Measurements

All the variables that will be recorded for each one of the patients included in the study are summarized in Additional file 1: Table S1.

Characteristics recorded at the time of transplantation include donor and recipient age and gender, body weight, height, body mass index (weight in kilograms divided by the height in meters squared), primary cause of renal failure (type I diabetes mellitus, type II diabetes mellitus, primary glomerulonephritis, nephrosclerosis including hypertension and renovascular disease, polycystic kidney disease, systemic lupus erythematosus, and others), cold ischemia time, type of dialysis prior to transplant (hemodialysis or peritoneal dialysis), total duration of renal replacement therapy before transplantation, and previous transplants. The date of transplantation and the type of donor (a deceased or living donor) will also be recorded.

Information about other traditional cardiovascular risk factors at the time of transplantation will also be collected, including history of tobacco smoking, hypertension, hypercholesterolemia, left ventricular hypertrophy, prior diabetes and a history of cerebrovascular disease (transient ischemic attacks and strokes), peripheral vascular disease (revascularization procedures and amputations) and malignancies prior to transplantation.

After transplantation, episodes of acute rejection and infections will be registered, together with the patient's smoking status, new-onset diabetes and diagnosis of left ventricle hypertrophy. Biochemical parameters will be collected during the post-transplantation follow-up at week 1, week 2, month 1, month 3, month 6, and yearly thereafter. These will include white blood counts, hematocrit, haemoglobin, cholesterol, high-density lipoprotein (HDL) cholesterol, low-density lipoprotein (LDL) cholesterol, triglycerides, creatinine levels and 24-hour proteinuria. At the same time intervals, systolic and diastolic blood pressure will be recorded. Renal function will be estimated using the Cockcroft-Gault formula [37] and the modified Modification of Diet in Renal Disease (MDRD) equation [38]. In the analysis of factors predicting new post-transplant cardiovascular events, the average of laboratory and blood pressure values recorded before the event will be considered.

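### Score validation names no in-scope subset, although the cohort is wider than the ranges the protocol itself gives for Framingham and SCORE

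*Protocol article*

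**What the plan says.** Under Design and study population, the Protocol article takes in "all adult (> 18 years) patients who underwent primary or repeated kidney transplantation". No upper age limit is given. The one exclusion stated there is: "Patients who had undergone simultaneous kidney-pancreas transplantation will be excluded from the analysis". Prior cardiovascular disease is not an exclusion. Under Measurements, the baseline data include "a history of cerebrovascular disease (transient ischemic attacks and strokes), peripheral vascular disease (revascularization procedures and amputations) and malignancies prior to transplantation", so recipients with earlier stroke or peripheral vascular disease are expected in the cohort.

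Under Quantification of cardiovascular risk, "Four established cardiovascular risk scores will be applied to the kidney transplant recipients at the time of transplantation". The same section then gives the scope of the tools. Both Framingham versions predict ten-year CHD risk "in adults between the ages of 30-74 with no known previous history of CHD, stroke, or peripheral vascular disease". SCORE estimates ten-year fatal cardiovascular risk "in subjects between the ages of 24 and 80". REGICOR and DORICA have no separate age or history range; the article says only that their "charts are adaptations of the Framingham equation to the Spanish population characteristics". The high-risk classification that closes the section is also applied to patients without restriction.

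Under Statistical analysis, the scores are assessed by the c index, time-dependent ROC curves, observed-to-predicted ratios and the Hosmer-Lemeshow test. No in-scope subset is named for any of these.

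**The concern.** The second objective asks how well established scores predict events in renal transplant recipients. The Background already reports that Framingham appears to underestimate event rates in these patients. A recipient aged 25, or one with a previous stroke, lies outside the Framingham scope as the protocol describes it, whether or not that person has a transplant. If such recipients enter the validation, two explanations for poor calibration are mixed: the score fails in transplant patients, or it was applied to people it was not built for. Recipients with prior disease would be expected to have higher event rates, which could push the observed-to-predicted ratio up and make Framingham look worse for a reason unrelated to transplantation.

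The comparison between scores is affected too. The stated age ranges differ (30-74 against 24-80), so in an unrestricted cohort the scores are extrapolated to different degrees.

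**Working it through.** **1. Cohort against stated scope**

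| Item | Cohort | Framingham | SCORE | REGICOR, DORICA |
|---|---|---|---|---|
| Age | over 18, no upper limit | 30-74 | 24-80 | not stated |
| Prior CHD, stroke or peripheral vascular disease | not excluded | none known | no condition stated | not stated |

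The cohort is wider than the Framingham range in both age and history, and wider than the SCORE range in age. For REGICOR and DORICA a limit can only be inferred from their Framingham origin.

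**2. The plan's own sample-size figure**

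Inputs from Sample size: relative risk 1.33, exposure prevalence 50%, censoring 78% (22% with events), power 80%. The two-sided 0.05 level is from Statistical analysis.

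Events = (1.960 + 0.842)² / (0.25 × ln(1.33)²) = 386.04 (Schoenfeld, unrounded z values).

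Patients = 386.04 / 0.22 = 1754.7, which reproduces the stated 1755. That figure concerns risk-factor regression in the whole cohort. Restricting the score validation does not change it.

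**3. Size of an in-scope validation set**

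The share q outside scope is not in the article. For assumed values of q, with 1794 patients and the 22% event proportion applied to those who remain:

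- Patients = 1794 × (1 − q); events = 0.22 × patients.

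| Assumed q | Removed | Remaining | Events |
|---|---|---|---|
| 5% | 90 | 1704 | 375 |
| 10% | 179 | 1615 | 355 |
| 20% | 359 | 1435 | 316 |
| 30% | 538 | 1256 | 276 |
| 40% | 718 | 1076 | 237 |

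If the excluded recipients have more events than the rest, fewer events would remain than shown.

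**4. Possible effect of prior disease on the observed-to-predicted ratio**

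Let s be the share with prior cardiovascular disease, m their observed event rate relative to the others, and r their predicted risk relative to the others. None of the three is in the article. The full-cohort ratio equals the ratio in the others multiplied by

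[1 + s(m − 1)] / [1 + s(r − 1)].

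| s | m | r | Factor |
|---|---|---|---|
| 0.10 | 2 | 1 | 1.10 / 1.00 = 1.10 |
| 0.10 | 2 | 1.5 | 1.10 / 1.05 = 1.05 |
| 0.20 | 3 | 1 | 1.40 / 1.00 = 1.40 |
| 0.20 | 3 | 2 | 1.40 / 1.20 = 1.17 |

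When r = m the factor is 1, so there is no distortion. The ratio rises only to the extent that the score fails to predict the extra risk. The formula does not cover out-of-range ages, and it says nothing about discrimination.

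**The case against.** The article never says that patients outside a score's range will be scored and kept in the validation. It refers to the kidney transplant recipients, and *all* is a reading of that phrase together with the cohort definition. Authors who set out applicability in the next paragraph may intend to respect it, and the make-up of validation subsets is often left to a fuller plan. Broad use may also be deliberate: the Background says validity in transplant patients is not well established, and the Discussion foresees prevention of both primary and recurrent events. Performance across all actual recipients is then a legitimate question.

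The second argument stands in part. The full-cohort result is worth having, so it should be reported alongside the in-scope result. It cannot, however, separate a transplant effect from use outside scope. The first argument does not remove the point: a wider cohort, an unrestricted application and a stated narrower scope stand together in the text, and the analysis section does not reconcile them.

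A reader might also infer that prior CHD is not collected, so that the Framingham limit could not be applied. The article does not support this. The list under Measurements is introduced as examples, and the full variable list is in Additional file 1: Table S1, which is not shown. Nor does the article support requiring freedom from prior cardiovascular disease for SCORE, since it gives only an age range.

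**Conclusion.** The point holds as a mismatch between the population scored and the scope the protocol states, most clearly for Framingham (age and history) and, on age alone, for SCORE. The consequence is limited interpretability: a poor observed-to-predicted ratio could be due partly to use outside scope.

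The size is not computable from the article. A reader might take inflation of 1.10 to 1.40 as the expected effect, but those values assume that recipients with prior disease have the same predicted risk as everyone else (r = 1). The scores use age, blood pressure, lipids and smoking, and the Framingham-type functions also use diabetes, so predicted risk in that group may well be higher. The illustrations with r = 1.5 and r = 2 give 1.05 and 1.17. All of these rest on assumed inputs.

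A reader might also conclude that the second objective goes unanswered. That is too strong: the unrestricted analysis still describes how the scores perform across recipients as they are.

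**What to change.** State the validation population for each score, and evaluate its calibration and discrimination in recipients within the scope the protocol itself gives:

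- Framingham (both versions): age 30-74 with no known CHD, stroke or peripheral vascular disease.
- SCORE: age 24-80.
- REGICOR and DORICA: the scope of their source functions, which should be stated.

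For each score, report how many recipients are excluded. Report the full cohort alongside, labelled as a separate analysis of performance in all recipients.

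The work is a paragraph of analysis wording and a flag built from age and recorded history. The price is a smaller in-scope validation set and so less precise estimates, as in step 3 of the working. No new recruitment is needed.

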### Sample size

During the study period (1981-2008) n = 2059 kidney transplants were performed in the A Coruña Hospital, corresponding to 1794 patients.

This sample size will make it possible to detect as significant, in a Cox regression model, a relative risk of 1.33 or more associated with a prevalence of exposure to a cardiovascular risk factor of 50% and a censored data percentage of 78% (Security: 95%; Statistical power: 80%). Assuming an exposure prevalence of 50% maximizes the sample size necessary to detect a relative risk of this magnitude. According to previously published data for this cohort of patients, the estimated incidence of CVD at five years is 22.2% [47], and so the censoring value was estimated at 78%. In this situation, the sample size required to estimate a relative risk of 1.33 or more (α = 0.05, β = 0.2) would be n = 1755 patients.

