The predictive performance of the nomogram will be evaluated by assessing both discrimination and calibration values [52]. A bootstrap re-sampling approach with 1000 replications will be used to reduce overfit bias. Discrimination will be quantified with the concordance c index and the area under the receiving operating characteristic (ROC) curve [50,51]. The nomogram will then be calibrated graphically, comparing the predicted probabilities with the actual rate of patients with cardiovascular events. A Loess curve will be fitted to the data and compared with an ideal fit. In addition, the Brier score will be calculated as a measure of the predictive accuracy of the model.

A p-value of < 0.05 will be considered as statistically significant (two-sided). Statistical analyses will be carried out with SPSS version 17.0 (SPSS Inc., Chicago, IL.) and R version 2.9.1 (The R Foundation for Statistical Computing), adding the ROCR, Design and Hmisc libraries.

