One of the limitations of this study is that information will mostly be taken retrospectively from hospital records, which could lead to information bias. On the other hand, transplant recipients are subjected to a more exhaustive follow-up than normal, not only during the immediate post-transplant period, but also during the years after the transplant. This fact would minimize any possible information bias. Likewise, during the study period standard immunosuppressive therapy has changed, and the treatment for each patient will depend on the date of transplantation and other medical subjective criteria. In order to control the changes that have occurred over the years, adjustments will be made based on the year of transplantation. Also, the therapeutic changes that occurred during the follow-up period for each of the patients will make it difficult to establish relationships between the medication and the cardiovascular events. Therefore, the impact of immunosuppressant medication on the presence of cardiovascular events in the follow-up could not be well established. The role of immunosuppressant agents must be investigated in greater detail with randomized clinical studies, and not with observational studies of this kind. However, our study will include a large cohort of patients with a long follow-up period, and the sample size is expected to be large enough both to identify individual CVD risk factors from multivariate analysis and to develop a new CVD prediction model.

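### The sample-size section calls 50% exposure prevalence the most demanding case, but under its own formula it is the least demanding, so 1755 is a minimum and not a conservative figure

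*Protocol article*

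**What the plan says.** The Sample size section starts from the available cohort: "n = 2059 kidney transplants were performed in the A Coruña Hospital, corresponding to 1794 patients". It says that a Cox model in this cohort can detect "a relative risk of 1.33 or more associated with a prevalence of exposure to a cardiovascular risk factor of 50" per cent, given 78% censoring. The censoring figure comes from earlier data on the same cohort: "the estimated incidence of CVD at five years is 22.2% [47], and so the censoring value was estimated at 78" per cent. The result is that "the sample size required to estimate a relative risk of 1.33 or more (α = 0.05, β = 0.2) would be n = 1755 patients".

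The only reason offered for choosing 50% is this sentence: "Assuming an exposure prevalence of 50% maximizes the sample size necessary to detect a relative risk of this magnitude".

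The Statistical analysis section fixes the test as two-sided at 5%. The Discussion closes with the expectation that "the sample size is expected to be large enough both to identify individual CVD risk factors from multivariate analysis", and that it will also support a new prediction model.

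**The concern.** In a Cox model the information on a binary covariate depends on how evenly it splits the patients. An even split is the most informative, so for a fixed relative risk an exposure of 50% needs the fewest patients. The article says the opposite. (For the precision of a single proportion, 50% is indeed the worst case, but that is a different calculation.)

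The sentence matters because it turns a result for one prevalence into an assurance for all. If 50% really were the worst case, a cohort slightly above 1755 would have at least 80% power for a relative risk of 1.33 at any prevalence. Finding factors related to cardiovascular events is part of the first objective. The Measurements section lists several binary candidates, such as prior diabetes, left ventricular hypertrophy and earlier cerebrovascular disease. A reader who relied on the sentence would credit the study with more power for an uncommon factor than it has.

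**Working it through.** **Inputs**
- Relative risk 1.33, exposure prevalence p = 0.50, 78% censored (event fraction 0.22), power 80%, α = 0.05: Sample size section.
- Two-sided test: Statistical analysis section.
- Patients available: 1794 (Sample size section).
- Other prevalences: assumed, because the article reports none.

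**Step 1: reproduce the stated figure.** The standard (Schoenfeld) formula for a binary covariate in a Cox model is

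events = (z₀.₉₇₅ + z₀.₈₀)² / [p(1−p)(ln RR)²], and N = events / 0.22.

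At p = 0.50: (1.960 + 0.842)² / (0.25 × 0.2852²) = 386.04 events, and 386.04 / 0.22 = 1754.7, which rounds up to 1755. This matches exactly. A one-sided test would give 1383, so the two-sided reading is the right one.

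**Step 2: vary the prevalence.** Everything except p(1−p) is constant, so N is proportional to 1/[p(1−p)]. The product p(1−p) peaks at 0.25 when p = 0.50, and N is therefore lowest there. For example, at p = 0.20 the events needed are 386.04 × 0.25/0.16 = 603.2, and N = 603.2/0.22 = 2742.

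**Step 3: power with the cohort in hand.** The expected events are 1794 × 0.22 = 394.7. Power = Φ(√[p(1−p) × 394.7] × ln 1.33 − 1.96). At p = 0.20: √(0.16 × 394.7) = 7.947; 7.947 × 0.2852 − 1.96 = 0.306; Φ(0.306) = 0.62.

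**Step 4: detectable relative risk at 80% power.** RR = exp[(1.960 + 0.842)/√(p(1−p) × events)], first with 394.7 events, then with an assumed 30% event fraction (1794 × 0.30 = 538 events).

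| Assumed prevalence | Events needed for RR 1.33 | Share of 1794 | N at 22% events | Power, 1794 patients, 22% events | Detectable RR, 22% events | Detectable RR, 30% events |
|---|---|---|---|---|---|---|
| 50% | 386 | 22% | 1755 | 81% | 1.33 | 1.27 |
| 30% (or 70%) | 460 | 26% | 2089 | 74% | 1.36 | 1.30 |
| 20% (or 80%) | 603 | 34% | 2742 | 62% | 1.42 | 1.35 |
| 10% (or 90%) | 1072 | 60% | 4874 | 40% | 1.60 | 1.50 |
| 5% (or 95%) | 2032 | above 100% | 9235 | 23% | 1.91 | 1.74 |

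At 40% or 60% prevalence power is 79%. Solving for power of at least 80% with 394.7 events gives prevalences from about 43% to 57%. The margin over the stated requirement is 1794 − 1755 = 39 patients, or 2.2%.

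**The case against.** Four points can fairly be made for the article.

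- **The explicit power statement is correct.** It ties 80% power to 50% prevalence, and 1755 reproduces. This stands: only the sentence about maximising, and the assurance it implies for other prevalences, is wrong.
- **The event count may be higher than 395.** The 22% is a five-year incidence, whereas the Measurements section follows patients to death or to renewed dialysis, in a cohort transplanted from 1981 onwards. Recent transplants and early losses pull the other way, and the final count is not given. This stands in part. About 26% of patients with events would restore 80% power at 30% prevalence, and about 34% would do so at 20%. At 10% it would take 60%, and at 5% more events than there are patients. Counting all 2059 transplants as independent units would widen the range with 80% power only to about 31% to 69%. No event count makes 50% the worst case.
- **Little in the study turns on it.** The cohort is every eligible transplant in a fixed period, so the calculation did not set its size, and the primary outcome is the estimation of cumulative incidence. That limits the consequence but does not make the sentence true.
- **Scope.** The grid applies to binary covariates. Many of the listed variables, such as age, blood pressure and lipids, are continuous, and the prevalence argument does not describe them. The Discussion remark is a general expectation and not a numerical claim.

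A reader might infer that the study lacks 80% power for most of its risk factors. The article does not support that, because it gives no prevalences. Nor does it support a recalculation after exclusions, because it reports no number excluded.

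**Conclusion.** The sentence is an error, shown by the article's own numbers, and no other section corrects it. The figure of 1755 is the smallest sample that meets the stated target, not a conservative one.

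With about 395 events, the shortfall in power for a relative risk of 1.33 is trivial at 40% or 60% prevalence, moderate at 30% or 70%, and serious at 20% or below and at 80% or above.

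This rests on the Schoenfeld approximation, which the exact match with 1755 supports; on the five-year event fraction; on assumed prevalences; and on a single unadjusted binary covariate. Correlation with other covariates in a multivariable model would lower power further, by an amount the article gives no basis to quantify. The conclusion is about a false statement in the justification and the assurance drawn from it. It is not a claim that the study is underpowered for its risk factors in general.

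**What to change.** In the Sample size section, replace the sentence on 50% prevalence with wording such as: *A prevalence of 50% minimises the required sample size. With 1794 patients and about 395 events, the relative risk detectable with 80% power is 1.33, 1.36, 1.42, 1.60 and 1.91 for binary exposures with assumed prevalence 50%, 30%, 20%, 10% and 5%. If 30% of patients have events, the corresponding values are 1.27, 1.30, 1.35, 1.50 and 1.74. These figures are for one unadjusted binary covariate.*

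In the Discussion, qualify the statement that the sample is large enough to identify individual risk factors, so that it refers to these detectable effects and says that power is lower for uncommon or very common exposures and in adjusted models.

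The cost is one sentence, a short table and a qualified claim. No patients, data or analyses change. The only downside is that the stated detectable effects become less favourable.
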